## Abstract

**Background:**

The MISAPSY study (Childhood Maltreatment, Food Insecurity, Psychological Distress and professional integration among socioeconomically disadvantaged young adults) aims to model the interrelations between child maltreatment, psychological distress and food insecurity, among precarious young adults enrolled in French integration services (Mission Locale). This population is exposed to multiple forms of social and material precarity. While food insecurity constitutes a tangible and increasingly prevalent dimension of precarity, it remains underexplored. By examining food insecurity alongside traumatic experiences and psychological distress, the study seeks to develop transferable explanatory models to inform the design of targeted prevention and support programs for young people in vulnerable situations.

**Methods/design:**

A triaxial methodology approach is implemented: (1) a cross-sectional study using standardized questionnaires to identify associated factors; (2) a qualitative study based on semi-structured interviews exploring psychologists’ subjective experiences of supporting these young people; and (3) a longitudinal comparative interventional study evaluates two different support programs (food aid only and combination of food aid and psychological support) for young adults enrolled in an insertion pathway. Outcomes include changes in psychological well-being and in food insecurity. Quantitative analyses will include descriptive and multivariate statistical tests using R, while qualitative data will be analyzed through thematic analysis with NVivo. Intervention effects will be examined using pre/post comparisons, mixed models, and appropriate statistical corrections.

**Discussion:**

This study is expected to highlight the high prevalence and interrelated nature of food insecurity, psychological distress, and traumatic experiences in this population. It is hypothesized that the combined intervention will show greater benefits for mental health status. MISAPSY aims to contribute to integrated, trauma-informed and food-security-oriented models to guide practitioners and policymakers in addressing the specific needs of socioeconomically disadvantaged young adults.

**Trial registration:**

This study is registered with the Biomedical Research Identification Number (n°ID-RCB) assigned in France by the National Agency for the Safety of Medicines and Health Products (ANSM): 2025-A01928-41, and have received the approval from the Committee for the Protection of Persons Ile-de-France XI and two Ethics Committees. This study was also registered on ClinicalTrials.gov on February 20, 2026 (NCT07427524). The full protocol and prespecified outcomes are publicly accessible through this registry.

**Supplementary Information:**

The online version contains supplementary material available at 10.1186/s40359-026-04292-0.

## Background

The Mission Locale (ML) is a French public institution designed to promote the professional and social integration of young people who encounter difficulties in the areas of employment, training, health or housing. Eligibility criteria for ML enrollment are: being aged 16–25 years; no longer being a student; encountering at least one difficulty related to the areas mentioned above, regardless of immigration status [1]. Beyond their primary objective of removing barriers to employment, these structures promote autonomy and independence. From a multidisciplinary professional perspective, MLs offer various programs related to education, training, schooling, health, social services and judicial prevention, within a holistic approach to the individual [2]. The trajectories of young adults supported by ML services are diverse but vulnerability factors are frequently observed, including school dropout, material insecurity, lack of employment or financial resources, multiple difficult life events in childhood and social isolation [3].

Young adulthood constitutes a transitional period marked by complex psychological adjustments, which can be hindered by adverse social contexts or significant crises. The global COVID-19 pandemic had a resounding and multifactorial impact worldwide [4] and led to an unprecedented increase in precariousness. In France, about 17% of 18–29-year-olds live below the poverty line and nearly half of poor people are under 30 years old [5, 6]. Youth in precarious situations frequently experience multiple psychosocial risk factors that affect their mental health. The deterioration of mental health among these vulnerable young people is a major concern, especially because the levels of depression and anxiety assessed in this population are notably high and continue to worsen [7, 8].

Food Insecurity (FI) can be defined as uncertainty about regular access to a sufficient quantity of food, of adequate quality to ensure a healthy and fulfilling life [9]. It is a tangible dimension of material precariousness. This increasing form of instability acts as a chronic stressor, due to an inability to meet basic needs [10, 11]. It has detrimental effects on psychological and emotional functioning. Regardless of levels of economic development, an analysis of data from 149 countries reports an increased prevalence of mental health disorders in contexts of moderate to severe FI [12]. Furthermore, a recent meta-analysis highlighted a significant association between FI and symptoms of depression, anxiety, perceived stress and sleep disorders [13]. Thus, FI appears to be one of the main social determinants of mental health, especially among 18–35-year-olds, showing strong associations with anxiety and depressive disorders and suicide risk, as highlighted by several studies [14–16]. In addition, FI has been identified as a predictor of child maltreatment within households [17].

The associations between low levels of food security and childhood maltreatment are bidirectional. Child abuse, which can take many forms, constitutes major Adverse Childhood Experiences (ACEs). The consequences of an accumulation of ACEs are numerous, including physical and mental health disorders, and can lead to premature death [18, 19]. Exposure to ACEs also increases the risk of experiencing FI in adolescence and adulthood. Certain forms of ACEs, such as emotional neglect, further exacerbate this risk, regardless of socioeconomic status [20, 21]. Childhood maltreatment, through its interpersonal nature, constitutes a potential precursor to the development of trauma, particularly in its complex form, which is linked to possible persistent alterations in the affective, relational and self-image spheres. It is also an identified risk factor for the emergence of other mental disorders that persist into adulthood [22–24]. In this research, we consider 5 types of ACEs: emotional abuse, physical abuse, sexual abuse, emotional neglect, physical neglect.

Thus, instability in food access cannot be understood solely as a social issue, although the socio-economic context is partly implicated. Precarious living conditions expose individuals to an increased risk of ACEs, FI, and psychological distress [25]. However, food security issues appear to be a major clinical determinant, likely explaining a substantial proportion of the mental health difficulties observed in this population.

While mental health has been designated a major national cause in France for the second year [26], the needs of vulnerable young people and their specific challenges remain largely overlooked, as issues of social and professional integration are only beginning to be linked to psychological well-being [2]. The level of care provided by ML stays highly uneven across different local branches. However, a program recently piloted in several French territories demonstrated that providing early psychological support within integration pathways can help prevent suicide risk, particularly among young people without active psychiatric follow-up [27].

In 2022, the ML of Paris (MLP) expressed the desire to explore interrelationships between child maltreatment, FI and psychological distress [28], in light of the impacts observed among their youth.

It appears essential to better understand the profound relationships between all these variables and to place basic needs at the core of care, as food deprivation constitutes a serious lethal risk and significantly contributes to the deterioration of mental well-being [29]. These considerations gave rise to the MISAPSY project (Childhood maltreatment, food insecurity, psychological distress and professional integration among socioeconomically disadvantaged young adults). Conducted at the University of Lorraine by researchers from the INTERPSY laboratory (UR4432), in collaboration with University of Paris Cité, this research examines the complex relationships between ACE, FI, and psychological distress among vulnerable young people enrolled in a professional integration program at the ML. The ultimate objective is to develop replicable models of understanding that can inform the design of support programs. This study focuses on a specific and understudied population: young adults in precarious situations, many of whom have faced adverse experiences and social exclusion. By positioning access to food as a central clinical determinant, the study examines its associations with ACEs and current psychological distress. By addressing the interconnections between material deprivation and mental health vulnerability in this population, the study aims to fill a significant gap in both research and practice.

In this article, we present the methodological characteristics of this research, which is built upon a solid institutional partnership framework and grounded in the contextual realities of the field, tailored to the specific needs of the target population. The study adopts a multidimensional approach, structured around three complementary components: a quantitative cross-sectional study, a qualitative study, and an intervention-based comparative longitudinal study. These methodologies aim to achieve several objectives: (1) To identify factors associated with FI and their connections to various aspects of mental health and ACE. (2) To conduct a review of psychologists’ practices in MLs and explore their subjective representations of psychological support. (3) To understand the impact of the type of ACEs on the life trajectories and how it influences FI severity. (4) To compare the effects of two different support systems by observing the evolution of FI and psychological distress among participants.

## Method/design

This research project is designed around three distinct methodological approaches. These phases are complementary (see: Table 1).

A cross-sectional study (study 1) based on a quantitative approach, consisting of the widespread distribution of standardized online questionnaires and scales (see: Measures) to young adults receiving support from any ML nationwide.The instruments facilitate a systematic collection of quantitative data and a multidimensional analytical framework to model the associations between psychological and social vulnerability factors. This design supports the identification of overarching statistical patterns.A qualitative study (study 2) intended for psychologists within MLs. This exploratory study offers a complementary perspective on understanding the experiences of youth at the MLs. By collecting data through verbatim analysis this study helps to identify some of the individual and institutional issues that influence the dynamics of care in these structures.An interventional longitudinal study (study 3) comparing two support programs. It is a multicenter, two-arm, parallel-group, single-blind randomized controlled trial. Participation is voluntary for young people experiencing severe FI and psychological distress, with a history of ACE, exclusively from MLP. The control group receives weekly food assistance for 12 months. The experimental group benefits from an intervention combining weekly food assistance for 12 months and twice-monthly psychological follow-up for 6 months. The study follows a superiority framework, hypothesizing that the combined intervention (food assistance plus psychological support) will lead to greater improvements in psychological distress and FI level compared to food assistance alone.

*Participants are assessed 4 times (T0: start of the program*,* T1: 3 months after the beginning*,* T2: end of the psychological intervention (6 months after the beginning)*,* T3: end of the program (12 months after the beginning). Each assessment period allows for the measurement of changes over time through standardized scales and semi-structured qualitative interviews. Detailed analyses will enable comparison of the specific effects of each intervention.*

**Table 1 Tab1:** Summary table of the research methodology

	Study 1	Study 2	Study 3
Type of study Method	Quantitative Cross-sectional study using self-administered questionnaires	Qualitative Semi-structured interviews	Longitudinal Intervention programs Self-administered questionnaires and semi-structured interviews
Eligibility criteria	Participant aged 18–25 Currently being supported by the Mission Locale	Being a psychologist Currently working at the Mission Locale Have at least one young adult in their active caseload	Participant aged 18–25 Currently enrolled in an insertion program in the Mission Locale Answer “yes” at item 8 of the FIES PHQ-9 score > 15 GAD-7 score > 10 exposed to one or more ACEs (CTQ-SF)
Exclusion criteria	Minors Do not speak and read French Under Guardianship or Curatorship Unable to provide informed consent	Not having psychological follow-up at the Mission Locale Unable to provide informed consent	Minors Do not speak and read French Under Guardianship or Curatorship Unable to provide informed consent Currently receiving psychiatric care for an acute or chronic mental illness requiring regular specialized treatment Presenting a social or medical emergency situation incompatible with the study Having already participated in a similar study or being currently engaged in a structured psychological intervention protocol
Main Outcomes	Food Insecurity prevalence Mental health aspects (anxiety, depression, PTSD and CPTSD) Childhood trauma Psychological resources (defense mechanisms, resilience, perceived social support) Substances use Quality of sleep	Psychological practice and working conditions Organization of care Perspective on the young people encountered Sensitivity to issues of trauma and vulnerability	Childhood trauma Mental health aspects (anxiety, depression, PTSD and CPTSD) Food Insecurity level Defense mechanisms Anamnesis, current living conditions, adherence and perception of interventions
Analysis	Quantitative analysis	Thematic analysis	Quantitative and qualitative analysis

### Participants

#### Study 1

Cochran’s formula (Z² × p × (1-p) / E²) was applied to determine the required sample size. We based our calculations on a population size of 180,000 young people supported during the previous year (N-1). The margin of error was set at 5%, with a confidence level of 95%. The required sample size for this cross-sectional study is therefore 384 respondents.

#### Study 2

Our qualitative study will include a sample of 15 volunteer psychologists from MLs, which is a number suitable for the Consensual Qualitative Research (CQR) method. Nevertheless, inclusion will continue until data saturation is reached. We will consider data saturation to have been reached when the analysis of a new interview reveals no new themes.

#### Study 3

To our knowledge, our study is one of the first to explore this approach in a structured and longitudinal manner. Considering the lack of comparable studies among precarious young adults we have adopted a pragmatic approach instead of a power calculation. We aim to include a total of 70 volunteer participants, or 35 people in each group.

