### Procedures

#### Study 1

Recruitment: A nationwide promotion will be launched across all MLs in France through the National Union of Local Missions (Union Nationale des Missions Locales: UNML) and the Regional Association of Local Missions (Association Régionale des Missions Locales: ARML). A flyer is designed to be sent out or displayed within the MLs. Each ML involved will send emails to registered young people. It includes detailed information about the research, a link to access the study and inclusion criteria (see: Table 1). Upon accessing the study’s homepage, participants will find an introductory note presenting the study, its objectives, a contact point for further information, and a link to open the questionnaire. This will lead to a consent form. To the question, “Do you consent to participate in this research?” participants will be able to answer “Yes” or “No.” Participants who select “Yes” access the questionnaire. Those who select “No” will not be able to continue.

#### Study 2

Recruitment: The qualitative study is addressed to psychologists currently working at the ML and having at least one young adult in their active caseload. A communication will be made by the UNML and ARML. After a presentation of the study by the researcher, the psychologists will receive an information sheet (see: supplementary material) detailing the study’s objectives, methodology, duration, constraints, and risks. The volunteer psychologists will then have 15 days to reflect and formalize their consent (see: supplementary material) by signing the dedicated form.Interview: After this period, each participant will be interviewed for a one-hour semi-structured session. The study can be conducted in person, via videoconference, or by telephone, according to the participant’s preference, but always under conditions that respect privacy. All interviews will be recorded using a voice recorder and will not collect any identifying data. The interviews will be transcribed, and the audio recordings destroyed after the topics have been validated by inter-rater agreement (according to the CQR method). Confidentiality will thus be guaranteed.

#### Study 3

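### Study 1's 5% margin of error holds only for a simple random sample, but respondents are volunteers reached through participating Missions Locales, so it does not bound the error of the food insecurity prevalence

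*Protocol article*

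**What the plan says.** The Study 1 paragraph of the Participants section starts from a formula for a single proportion: "Cochran’s formula (Z² × p × (1-p) / E²) was applied to determine the required sample size". It takes 180,000 young people supported in the previous year as the population, then fixes precision: "The margin of error was set at 5%, with a confidence level of 95" per cent. The conclusion follows directly: "The required sample size for this cross-sectional study is therefore 384 respondents". No value of p is given, and no allowance for clustering or non-response is mentioned.

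The Study 1 paragraph of the Procedures section describes how respondents are found. "A nationwide promotion will be launched across all MLs in France", through the national union and the regional associations. "A flyer is designed to be sent out or displayed within the MLs". "Each ML involved will send emails to registered young people". The material describes the research and carries a link. Whoever follows it and consents enters the questionnaire. No random draw from a list of supported young people is described.

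Table 1 names "Food Insecurity prevalence" first among the main outcomes of Study 1.

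**The concern.** The sample size section and the recruitment section describe two different kinds of sample. Cochran's formula gives the sampling error of one proportion when each member of the population is equally likely to be drawn, independently of the others. The recruitment route departs from that in two ways:

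- **Clustering.** Respondents arrive in groups through the MLs that forward the email or show the flyer. If food insecurity varies between MLs, 384 respondents carry less information than 384 independent draws.
- **Self-selection.** Young people decide whether to answer after reading what the study is about. If that decision is related to food insecurity, the respondents' prevalence differs from that of the 180,000, and the margin of error does not show it.

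At stake is what Study 1 can say about a listed main outcome. The abstract expects a high prevalence of food insecurity and wants the project to guide practitioners and policymakers. A prevalence quoted with plus or minus 5 points for supported young people would claim more than the design can give.

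**Working it through.** **1. The plan's own figure.** From the Participants section: E = 0.05, 95% confidence (Z = 1.96), N = 180,000. Assumed: p = 0.5, the worst case.

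- n0 = Z² × p(1−p) / E² = 1.96² × 0.25 / 0.0025 = 384.15
- With finite-population correction: 384.15 / (1 + 383.15/180,000) = 383.3, rounded up to 384
- Margin at n = 384 under simple random sampling: 1.96 × √(0.25/384) = 5.0 points

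The stated 384 is reproduced.

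**2. Clustering.** The article gives no number of MLs, respondents per ML or intracluster correlation (ICC). Assumed ranges: k = 20 to 100 MLs with equal numbers of respondents, ICC = 0.02 to 0.10.

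- Respondents per ML: m = 384/k. Design effect: DE = 1 + (m−1) × ICC. Effective sample size: 384/DE. Margin: 1.96 × √(p(1−p) × DE/384).

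| Case | m | DE | Effective n | Margin, p = 0.5 |
|---|---|---|---|---|
| Mild: k = 100, ICC 0.02 | 3.84 | 1 + 2.84 × 0.02 = 1.06 | 363 | 5.1 points |
| Severe: k = 20, ICC 0.10 | 19.2 | 1 + 18.2 × 0.10 = 2.82 | 136 | 8.4 points |

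The margin also depends on p. At p = 0.8 (or 0.2) with DE = 1.5 it is 1.96 × √(0.16 × 1.5/384) = 4.9 points, still inside the target. At that prevalence, a DE up to about 0.25/0.16 = 1.56 is absorbed.

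**3. Self-selection.** Let r be the response rate of food-insecure young people divided by that of the others. The article gives no r, so the values are assumed. The expected prevalence among respondents is q = pr / (pr + 1 − p).

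| True p | r | q | Bias |
|---|---|---|---|
| 50% | 1.25 | 0.625/1.125 = 55.6% | +5.6 points |
| 50% | 1/1.25 = 0.8 | 0.40/0.90 = 44.4% | −5.6 points |
| 50% | 1.5 | 0.75/1.25 = 60.0% | +10 points |
| 30% | 1.25 | 0.375/1.075 = 34.9% | +4.9 points |

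At p = 50%, the bias reaches the full 5 points once q = 55%, that is r = 0.55/0.45 = 1.22, or its inverse.

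Coverage of the nominal 95% interval at p = 50%, r = 1.25: the standard error is √(0.556 × 0.444/384) = 0.0254, the bias is 0.0556/0.0254 = 2.19 standard errors, and coverage is about 41%. At r = 1.5 it is about 2%. A larger sample does not remove the bias; it only narrows the interval around the wrong value.

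**The case against.** The other side has several fair points.

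- **The 5% is a planning input.** The article does not tie it to food insecurity prevalence or promise a plus or minus 5-point interval in the results. Study 1 is framed largely around associations, with correlation, factor and network analyses that depend less on this margin. This limits the weight of the point but does not remove it: the formula is for a proportion, and food insecurity is the only main outcome of Study 1 expressed as a prevalence.
- **The size of any clustering is unknown.** Promotion goes to all MLs, so many could contribute a few respondents each and the design effect could be close to 1. A prevalence far from 50% gives further room. The Background's remark that the level of care differs between local branches concerns services and does not show that food insecurity differs by ML. This stands. The documents do not support the stronger reading that the true margin must exceed 5 points.
- **The direction of self-selection is unknown.** A reader might infer that prevalence will be overestimated because the topic attracts those affected. The most deprived may equally be less able to answer an online questionnaire. This stands, which is why the working shows both signs.
- **The listed tests are examples.** A reader might infer from the Data analysis section that ML will be ignored. That list is openly illustrative, the sociodemographic items are not itemised, and the full analysis plan is not shown. No omission in the analysis can be claimed.

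None of this answers the core. An analysis plan can adjust an interval, but it cannot turn volunteers into the random sample that the stated margin presupposes.

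**Conclusion.** The point holds as a mismatch between a formula's sampling assumption and the recruitment described. It is not an arithmetic error: 384 is correct for what the formula calculates, and a reader who concluded that the number was miscalculated would be wrong.

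The stated 5% at 95% confidence is nominal. It does not bound the error of the food insecurity prevalence as an estimate for the 180,000 supported young people. Self-selection is the stronger limb: a response ratio of about 1.22 in either direction is enough, at a true 50%, to produce a bias as large as the whole margin. Clustering is the weaker limb, from negligible to 8.4 points over the ranges tried at p = 0.5. All sizes rest on assumed response ratios, ML numbers and ICCs.

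Study 1 is not invalidated. The change is worth making because it is cheap and alters what can be concluded about a listed main outcome.

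**What to change.** - **Participants, Study 1:** state that 384 gives a nominal plus or minus 5% at p = 0.5 under simple random sampling only, before any effect of clustering or selection.
- **Questionnaire:** make sure each respondent's ML is recorded, if only as a coded cluster identifier. It should be collected at response, because the data are later stripped of identifying information.
- **Analysis:** compute the confidence interval for food insecurity prevalence with standard errors clustered by ML.
- **Reporting:** present the estimate as prevalence among respondents, not among all supported young people.
- **Optional:** if the ML network can supply age, sex and region totals, add a weighted estimate as a sensitivity analysis. The article does not say that such totals are available, and weighting to them would not remove selection on food insecurity itself.

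The cost is one questionnaire item if the ML is not already recorded, a few sentences of text, and a slightly less favourable stated precision.
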